**Figure 1 F1:**
[figure not shown]
**Flow diagram of the trial design**.

### Setting

The study will be carried out in 30-50 general practices around two centres (the department of Audiology at King Edward VII Hospital in Berkshire and the University of Southampton), to sample differing existing models of delivery of routine primary and secondary care. These general practices will be sampled to include urban, suburban and rural practices with varying levels of social deprivation. Telephone support will be provided by vestibular therapists based at the two centres, and data will be collected centrally at the University of Southampton.

### Sample size/power calculation

Assuming that we will achieve a treatment effect at least as great as that in our last primary care trial (d = .41) [42], we will need 95 patients per group to test a two-tailed hypothesis with 80% power and 5% significance level. Drop-out at six months in our previous primary care trial was 8.8% (and only 4.7% in our previous self-treatment trial), but since we have a longer follow-up we will allow for 15 patients to drop out of each condition (14.25%), giving a sample size of 110 in each condition (a total of 330).

This sample size should be attainable in practice, as the two previous primary care trials using similar recruitment methods and recruitment time scales (15 months) were able to attain comparable sample sizes. Yardley and colleagues [41] identified 327 eligible patients from 10 general practices of varying size, from which 115 were recruited into the trial. Our last primary care trial [42] also followed the same time scale and recruitment method, contacted approximately 680 participants at 20 general practices and recruited 170 participants. Based on these numbers we would expect to contact between 981 and 1700 patients from 30-50 general practices to recruit approximately 255 - 575 participants into the trial.

### Participant recruitment and selection

Potential participants will be identified by practice staff (with the help of a research associate who will hold honorary contracts with the PCTs) searching the computerised database of the practice. The computerised database search will follow inclusion and exclusion screening criteria that proved successful in previous primary care studies of dizziness to safely and effectively identify patients likely to benefit from the self-help exercises [41,42]. We have support for patient recruitment from the Primary Care Research Network South East, South West and Western branches, and will therefore receive service support costs for general practices taking part. Patients can also be directly identified by their general practitioner, and posters will be displayed in practices to inform patients that they can ask to participate.

Eligible patients will be sent a letter and invitation pack (including the information sheet and consent form) from their GP inviting them to take part. Patients who do not wish to take part in the trial but are happy to provide further information are invited to complete a trial refusal slip indicating whether they are a) no longer dizzy, b) dizzy but feel that the treatment would not be suitable for them, c) dizzy but do not want to take part in the trial because the support is given over the telephone, and the patient has hearing difficulties, or d) do not want to take part in the trial for some other specified reason. Patients who have consented to take part in the trial will receive a copy of their signed consent form (also signed by the research associate). The research associate will also keep a copy for the trial file, and then send the original to the patient's GP practice for inclusion with the patient's medical notes. After baseline questionnaire assessment, patients will be excluded prior to randomization if they report that they are no longer dizzy, or their dizziness is not aggravated by performing head movements (in which case their dizziness is not typical of vestibular imbalance and is unlikely to respond to the self-help exercises). All respondents will receive a group allocation letter, explaining which treatment group they have been assigned to, or explaining that they have not met the inclusion criteria.

#### Inclusion criteria

a) Patients must be 18 or over and registered at a participating general practice.

b) Patients must have seen their GP for dizziness some time in the past two years (Participating practice computerised databases will be searched using search terms such as: vertigo; dizziness; Meniere's disease; balance problems; vestibular; prochlorperazine; cinnarizine; betahistine; diuretics - terms used will vary according to how patient data is recorded by the practice).

c) Patients must return the completed and signed consent form

d) Patients must indicate in the baseline questionnaire assessment that they still experience dizziness and that quick head movements make them dizzy.

#### Exclusion criteria

a) Non-labyrinthine cause of dizziness identified by GP (in which case patients will not benefit from the vestibular rehabilitation exercises)

b) Medical contraindications for making normal head movements (e.g. severe cervical disorder), in which case patients will be unable to carry out the exercises.

c) Serious co-morbidity (e.g. progressive central disorder, terminal illness, and moderate to severe dementia or mental illness).

d) Moved away from practice

e) Recently deceased

f) Non-English speakers and people unable to read and write English.

### Randomization to treatment groups and blinding

Eligible patients who have signed a consent form to take part will be randomised by an administrative assistant at the University of Southampton with no prior contact with the patient. The assistant will use a remote randomisation service, such as the Trans European Network for Clinical Trials Services (TENALEA), to generate a schedule for assigning participants on the basis of block randomization within practice (block size 9) after stratification for severity of symptoms (score below 12 or 12 and above) on the main outcome measure at baseline. To ensure that centre effects are not confounded with therapist effects, patients will be randomised to the three treatment groups and to the three therapists. The research associate collecting the data will remain blind to patient allocation until after the 12 week follow up. The research associate will then become unblinded to the name and group allocation of a small subsample of participants who are taking part in interviews of their experiences of using the self-treatment booklets and telephone-based therapist support. The research associate will not become unblinded to these participant's trial number, which is the only identifier by which outcome data are identified. The statistician analysing the data will remain blind to patient allocation throughout the trial. Blinding of patients is not possible due to the nature of the therapy.

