### Management of trial fidelity

The design of the trial is intended to minimise centre, therapist and practice effects on outcome. Randomisation is at the level of the individual participant rather than practice, since contamination is improbable (in theory, participants receiving the booklet could show it to those who did not receive it, but it is highly unlikely that they would come into contact and discuss the trial and treatment). Practice effects are further minimised by detailed guidance from the research team regarding inclusion and exclusion criteria for patients to be invited to participate. Since there will be numerous referring practices from each centre, centre effects on clinical outcome should not be significant.

Although the trial intervention is within the routine professional competence of the three VR therapists, therapist effects are minimised by strict manualisation of treatment. The VR booklet forms the basis of treatment, and the therapist's role is simply to ensure that the patient understands and follows the booklet correctly, and to answer questions and respond to concerns. Telephone support will be standardised using a written workshop format with example patient case scenarios published with the paper reporting the previous trial [42]. The content of each therapist session is specified by a checklist. All telephone support sessions will be tape-recorded, and the research associate will examine treatment fidelity by comparing therapist checklists with a sample of taped sessions to determine the accuracy of reporting completion of the treatment protocol. Therapist effects are also likely to be minimised by the absence of personal contact or an ongoing professional relationship between the therapist and patient.

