#### Stopping rules

Since the exercises do not require any unusual or strenuous movements, the risks of carrying them out are very slight. Nevertheless, there is a remote possibility that the exercises could bring on symptoms that could signal the potential for serious medical consequences, specifically cervical damage, damage to the inner ear (perilymph fistula), or vertebrobasilar ischaemia. These symptoms, which are detailed in the information sheet and in the self-help booklet, are:

• A sharp, severe or prolonged pain in the neck, head or ear

• A feeling of fullness in the ear

• Deafness or noises in the ear

• Fainting with loss of consciousness or blacking out

• Double vision

• Numbness, weakness or tingling in the arms or legs

In the very unlikely event that a participant experiences these symptoms, they are advised (in the information sheet, group allocation letter and self-help booklet) to stop the exercises immediately, and consult their vestibular therapist if in the telephone support group, or the research associate if in the booklet without support group. Problems are usually managed by advising participants to do the exercises more slowly and gently (i.e. usually the problems are just some non-serious aggravated neck pain or dizziness). If thought to be necessary, participants will be referred to their GP; however, this has not been necessary in our previous clinical trials, and other clinical trials of VR have also reported no adverse effects as a result of undertaking VR [25].

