### Data collection and follow up

Participants in all three treatment arms of the trial will be sent, by post, questionnaire packs (and a freepost return envelope addressed to the research associate) to complete at baseline, 12 weeks after being allocated to a treatment group, and at one year follow up. The baseline and one year follow up questionnaires should take approximately up to 20 minutes to complete, and the 12 week follow up questionnaire should take approximately up to 25 minutes to complete.

Self-report of service use (GP visits, medication, referral etc.) will be checked by the research associate for accuracy against the medical records in a random sub-sample of at least 20 percent of patients. If significant discrepancies between records and patient reports of service use are found then a larger proportion will be checked if time permits.

To incorporate representation of patients' views of the trial into our evaluation, telephone-based interviews will be conducted with 24 - 30 participants; 12 - 15 participants from the booklet only condition and 12 - 15 from the booklet with therapist support condition. These will take place after completion of the 12 week questionnaire, and will last approximately 30 minutes. The interviews will explore participants' experiences of using the self-treatment booklets and telephone-based therapist support.

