#### Non-responders and drop out from the trial

Non-responders to the baseline, 12 week and one year follow up questionnaires will receive one postal reminder after 3 weeks, and a follow-up telephone call (with collection of data by phone interview if preferred) for those who still do not respond after a further 3 weeks. Dizzy patients who volunteer to participate are typically well-motivated to adhere to trial procedures; in our last trial we used postal measurement of outcomes, and only 17 patients out of 360 failed to complete the final follow-up [43]. Participants who have chosen to drop out of the trial are asked in the reminder letter to return the questionnaire unanswered, so that we know that they do not want receive the telephone reminder or further information about the trial. Participants can either withdraw from the trial entirely, or may choose to withdraw from carrying out the exercises in the self-treatment booklet but still continue to complete the follow up questionnaires. Participants remain free to drop out of the trial at any stage, and will not be replaced if drop out occurs after randomisation. Follow-up by telephone of non-respondents will be carried out by the blinded research associate; patients will be advised not to reveal their trial status, and any failure of blinding will be recorded and potential effects on trial outcomes analysed.

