### Outcome measures

The measures used at each data collection point are summarised in Table 1. For comparability with the previous trials of the self-help booklet, the primary outcome measure will be self-reported symptoms of dizziness, assessed by the Vertigo Symptom Scale - Short Form [46], which assesses frequency of fifteen dizziness-related symptoms during the past month on a five point scale. A recent study has suggested that the Vertigo Symptom Scale - Short Form has a stable and reliable two factor structure, relating to vertigo and autonomic anxiety [47]. As it is of clinical interest to be able to discriminate between symptoms resulting from vertigo and secondary symptoms due to autonomic anxiety, these subscales will therefore be explored as secondary outcomes.

**Table 1 T1:** Measures used in baseline, 12 week and one year follow-up questionnaires.

Measure	Baseline	12 week	One year
Demographic characteristics	X		
Duration of current symptoms	X		
Diagnosis received	X		
Dizziness due to head movements	X		
Vertigo Symptom Scale - Short Form (VSS-SF)	X	X	X
Dizziness Handicap Inventory (DHI)	X	X	X
Hospital Anxiety and Depression Scale (HADS)	X	X	X
Management of dizziness (consultations in primary and secondary care and other sources; hospital stays; medication/treatment; days off work)	X		X
Quality of Life (EuroQoL - EQ-5D)	X	X	X
Your dizziness or unsteadiness now		X	X
Problematic Experiences of Therapy Scale (PETS; booklet arms only)		X	
Adherence to therapy (booklet arms only)		X	
Total time spent on each exercise (booklet arms only)		X	
Continuation of therapy (booklet arms only)			X

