### Statistical analysis

Data entry will be carried out by the administrative assistant and double checked by the research associate. The trial will be analyzed on an intention to treat and per protocol basis, using SPSS for Windows (SPSS Inc., Chicago) and Stata (StataCorp). Levels of missing data will be investigated, but are expected to be very low for the primary outcome (see above). Missing data on individual items on scales used to measure secondary outcomes will be replaced by the blinded research associate by the mean for that individual on that scale, provided that the majority of items have been completed. Where relevant, outcome variables will be checked for the assumption of normality. If the assumption is not met, data transformations or equivalent non-parametric tests will be conducted. Effect sizes and confidence intervals will be reported for all tests.

Qualitative methods will be used by the research associate to examine treatment fidelity by comparing therapist checklists with a sample of taped sessions to determine the accuracy of reporting completion of the treatment protocol. The research associate will also use qualitative methods to analyse the interviews of participants' experiences of using the self-treatment booklets and telephone-based therapist support.

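### The research associate is described as blind but is given tasks that disclose allocation, so the blinding statement cannot be carried out as written

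*Protocol article*

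**What the plan says.** Patients cannot be blinded, so the single-blind label rests on the research associate and the analysts. On the research associate, the protocol article (Randomization to treatment groups and blinding) says: "The research associate collecting the data will remain blind to patient allocation until after the 12 week follow up". It allows one later exception: "The research associate will then become unblinded to the name and group allocation of a small subsample of participants", namely those interviewed, whose trial numbers stay hidden from the research associate.

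The same person has these tasks elsewhere:

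- Data collection and follow up: participants are sent "questionnaire packs (and a freepost return envelope addressed to the research associate" at baseline, 12 weeks and one year.
- Outcome measures, Table 1: the 12-week pack includes "Adherence to therapy (booklet arms only", along with a therapy-problems scale and exercise times under the same restriction. The one-year pack has an item on continued therapy, also for the booklet arms only.
- Statistical analysis: "Data entry will be carried out by the administrative assistant and double checked by the research associate".
- Stopping rules: participants with listed warning symptoms are told to "consult their vestibular therapist if in the telephone support group, or the research associate if in the booklet without support group".
- Management of trial fidelity: "the research associate will examine treatment fidelity by comparing therapist checklists with a sample of taped sessions".
- Non-responders and drop out from the trial: "Follow-up by telephone of non-respondents will be carried out by the blinded research associate".

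**The concern.** In an open-label trial with a self-reported outcome, blinding of the person who chases, receives and checks the data is one of the few protections left, and readers will judge the trial partly on it. Here the protection is stated firmly in one section and undone by duties assigned in others. Two things are at stake: whether the description of blinding is true, and whether knowledge of arm could affect the outcomes in which the research associate has a live part. Those are the scores obtained by telephone from people who did not return a questionnaire.

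**Working it through.** The plan gives no figure to reproduce on this point. The check is to set each duty of the research associate against the blinding statement and ask what it discloses, for whom and when.

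**1. Returned packs.** With 110 participants per arm, 2 × 110 = 220 are due the booklet-only sections at 12 weeks and 110 are not. A pack with those sections filled in comes from a booklet arm; a pack without them comes from routine care. The main analysis compares booklet plus telephone support with routine care, so this is enough to separate its two sides. It does not separate the two booklet arms. The continuation item discloses the same thing at one year. Double-checking of data entry brings the research associate back to the same content.

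*Timing:* at 12 weeks the disclosure arrives with the completed outcome. One could argue that the phrase about remaining blind until after that follow-up is then nearly met. But the next sentence limits later unblinding to interviewees, and the non-responder section still calls the research associate blinded without restricting this to 12 weeks.

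**2. Symptom contacts.** The stopping rules send booklet-only participants to the research associate and supported participants to their therapist. A contact by this route reveals the exact arm, and it happens during treatment, before the primary outcome is measured. This directly contradicts the blinding statement for anyone who makes such a contact. The section on the unsupported booklet names the research team in general instead, so the two sections also need reconciling with each other.

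**3. Tapes.** Support sessions exist only in the telephone-support arm, so any identifiable tape discloses that arm. Only a sample is reviewed, and neither timing nor labelling is stated. Whether this happens before outcome collection ends is therefore open. Even a late review falls outside the single exception the blinding section allows.

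**4. Where knowledge of arm could reach an outcome.**

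- *Postal scores at 12 weeks:* completed before the research associate opens the envelope. What remains is the data check.
- *Telephone scores at 12 weeks:* the person called has not returned the revealing pack. Prior knowledge would come from an earlier symptom contact, or from a tape if review is early.
- *Telephone scores at one year:* the research associate may by then have seen that participant's 12-week pack. This is the widest route. It assumes that whoever chases a named non-responder can connect that person with the trial number. The article does not say so, but chasing seems to require it.
- *Item imputation:* a fixed person-mean rule, for secondary scales only, so there is little room for judgement.

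**The case against.** The strongest reply is that the harm is small. The primary outcome is mostly postal self-report. Telephoned 12-week non-responders have not sent a pack. The listed symptoms are expected to be very rare. The tape review may come late. The analysts stay blind throughout. For telephone follow-up, patients are asked not to reveal their group, and failures of blinding are to be recorded and their effect analysed. All of this stands, and it limits the consequence.

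It does not remove the contradiction. The telephone safeguard deals with accidental disclosure in a call, not with disclosure built into the packs and the contact route. Hiding trial numbers covers interviewees only.

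Several stronger readings are tempting and not supported:

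- *That up to 330 outcomes are at risk because every pack is revealing.* That counts disclosures, not outcomes that could be altered.
- *That the research associate can shade missing primary-outcome items.* The imputation rule is fixed and is stated for secondary scales.
- *That the interviews breach the blind.* They are openly declared and take place after the 12-week questionnaire, so they cannot affect the 3-month primary analysis. They involve 24 to 30 of 220 booklet-arm participants (24/220 = 10.9%; 30/220 = 13.6%), and only those who also need a one-year call would matter.
- *That the trial has no blinding at all.* The analysts' blinding is not in question.
- *That a size can be computed.* If 10 to 15% of outcomes came by telephone with a 2-point arm-dependent shift, the arm difference would move by 0.10 × 2 = 0.2 to 0.15 × 2 = 0.3 points, against the plan's 3-point threshold for clinically significant change. Both inputs are assumptions without support in the article, and the sum presumes the caller knows the arm every time.

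**Conclusion.** The point holds as an internal contradiction. The blinding described for the research associate cannot be kept alongside the pack contents, the data check and the symptom-contact route, and the tape review adds a further, undated exposure. Disclosure of booklet versus routine care is systematic through the packs; disclosure of the exact arm before 12 weeks is confined to those who make symptom contacts.

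The risk of bias is limited. It sits mainly in telephone-collected outcomes, chiefly at one year after the 12-week packs have been seen, and in 12-week calls to participants who made an earlier symptom contact. No reliable size can be given from the document. The conclusion does not depend on the research associate acting on the knowledge, only on the duties as written. The one-year route further assumes that the caller can link person and trial number.

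**What to change.** - Put the booklet-only sections, at 12 weeks and one year, in a separate insert returned to the administrative assistant, who carries out the randomisation and arranges the therapist calls and so is already unblinded. Exclude these sections from the research associate's data check until outcome collection is complete.
- Reconcile the stopping rules with the blinding section so that arm-specific symptom contacts do not go to the blinded data collector. Who takes them is for the sponsor to decide; the clinical advice is outside this point.
- State that the tape review follows outcome collection.
- Do not hand one-year outcome calls to the administrative assistant. That would replace a partly unblinded caller with a fully unblinded one.

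If these changes are not made, reword the blinding and non-responder sections so that only the analysts are called blind and the research associate is described as partly unblinded.

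The cost is a small change to the packs and participant letters and a later fidelity check.
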